## Abstract

**Background:**

Cardiovascular disease, endothelial dysfunction, and oxidative stress are common complications among patients with type 2 diabetes (T2DM). In addition to the average blood glucose concentration, glycemic variability may be an important factor for the development of chronic diabetes complications. Patients with T2DM are treated with various types of oral glucose-lowering drugs. Exercise is considered to benefit the health of both healthy and unhealthy individuals, which has been confirmed by a number of scientific research studies in which the participants’ health improved. Our general aim in this study will be to evaluate glucose variability after submaximal exercise test in patients receiving treatment with either vildagliptin or glibenclamide. The specific aims of this study are to evaluate the oxidative stress, endothelial function, and metabolic and cardiovascular responses to exercise under treatment with vildagliptin or glibenclamide. All these responses are important in patients with T2DM.

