## Background

Cardiovascular disease is the main cause of mortality among people with type 2 diabetes mellitus (T2DM) [1, 2]. Accelerated atherosclerosis in these patients is preceded by endothelial dysfunction, inflammatory burden, and increased lipid peroxidation, all leading to enhanced macrophage foam cell formation [2]. In addition to the average blood glucose concentration, acute glycemic fluctuations from peaks to nadirs (glucose variability) may be involved in the development of diabetic complications [3], as they contribute to the generation of excessive protein glycation and oxidative stress [4]. High glucose variability has been shown to be associated with endothelial dysfunction in patients with T2DM and optimal metabolic control [5]. Currently, the mean amplitude of glycemic excursion (MAGE) is one of the most used methods for detecting significant swings in glycemia [6], but other tools may be useful to identify disturbances in glucose variability [7].

Some current treatments for T2DM have already been tested concerning their possible effects in reducing glucose variability as well as reducing glycated hemoglobin (HbA1c) [8]. Exercise, which is one of the cornerstones of treatment for hyperglycemia in T2DM because of its beneficial effect on HbA1c [9], was recently shown to reduce glucose variability in addition to its acute effects on reducing glucose levels [7]. Vildagliptin and sitagliptin are two drugs that were recently evaluated in a study focusing on possible differences in daily glucose fluctuations in patients with T2DM inadequately controlled with metformin, and it showed that vildagliptin was more effective in flattening acute glucose fluctuations over a day [8]. Moreover, acarbose was superior to glibenclamide in reducing MAGE. Therefore, aside from their absolute glucose-lowering effect, it is evident that other effects of different anti-diabetic agents might also be different [10].

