The present study will be conducted to test the hypothesis that in combination with metformin, vildagliptin may produce a greater improvement in glucose variability after a submaximal exercise test, compared with glibenclamide. Our general aim will be to evaluate glucose variability after the submaximal exercise test in patients receiving treatment with vildagliptin or glibenclamide. The specific aims of this study are to evaluate the oxidative stress, endothelial function, and metabolic and cardiovascular responses to exercise in patients treated with vildagliptin or glibenclamide.

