### Sample size calculation

According to data reported by Marfella *et al*. [8], a total sample size of 20 patients (allowing for a dropout rate of 10%) should allow detection of a difference between groups with MAGE levels (mean ± SD) of 25.0 ± 16 mg/dl at week 12, assuming statistical power of 90%, and a significance level of 1% (two-sided, two-sample *t*-test).

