### Glucose variability evaluation

CGMS will be utilized for this evaluation. Subjects will be admitted to the laboratory in the morning at approximately 08.00 hours, 24 hours before the exercise session, when the glucose sensor (Sof-SensorTM; Medtronic Mini-Med Inc., Northridge, CA, USA) will be inserted subcutaneously. The sensor is a glucose oxidase-based platinum electrode that is inserted through a needle into the subcutaneous tissue of the anterior abdominal wall, using a spring-loaded device (Senserter, Medtronic Mini-Med Inc.).

Glucose oxidase catalyzes the oxidation of glucose in the interstitial fluid, which generates an electrical current. The current is carried by a cable to a pager-sized monitor that analyzes the data every 10 seconds and reports average values every 5 minutes, to give a total of 288 readings per day. Glucose profiles will be collected on the day before (day 1), the day of (day 2), and the day after (day 3) the submaximal exercise test. Sensor readings will be calibrated with a glucose monitor (Accu-Check Performa; Roche Diagnostics) using four finger-stick blood samples for each 24 hours. Each sensor will be used continuously for up to 48 hours. All patients will have been instructed previously about the operation of the monitor, which includes event registration for meals, and inserting capillary glucose values for calibration.

Glucose variability will be assessed from a series of absolute values of glucose, obtained by the CGMS, sampled every 5 minutes. Each method will be used as reported in the literature and according to its limitations. Glucose variability will be evaluated using conventional analysis and other mathematical methods generally applied to biological series, here called “non-conventional analysis of glucose variability.” Conventional analysis of glucose variability will be constructed from the statistical properties of the series, to obtain the following indices: MAGE [6], glucose variance (VAR), glucose coefficient of variation (CV%), and glucose SD, all normalized by the mean blood glucose in each period [15, 16]. These indices, except MAGE, will be calculated for every 6 hour block of glucose values to obtain the measures according to the specific period of the day. The MAGE index will be calculated for the whole signal (24 hours), and its calculation is based on the differences between consecutive points, considering those which are higher than 1SD [16].

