Non-conventional analysis of glucose variability will be conducted using two methods applied to the glucose series: a linear method based on spectral analysis, and an integrated non-linear approach to the complexity analysis, called symbolic analysis. Spectral analysis is a linear method that allows quantification of the oscillatory components from time series by autoregressive models widely applied for heart rate and arterial pressure series [17]. Symbolic dynamics relies on the calculation of Shannon entropy of the distribution of patterns lasting three measures and the classification of frequent deterministic patterns lasting three measures, and distributes deterministic patterns of the group into four categories according to the number and pattern: 1) no variation (0 V), 2) one variation (1 V), 3) two like variations (2 LV), and 4) two unlike variations (2 UV) [18]. This method has been fully described and validated previously to glucose curves [7].

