### Statistical analysis plan

Data will be analyzed using SPSS software (Statistical Package for Social Sciences; version 18.0 for Windows, SPSS Inc., Chicago, USA). The description of values will be expressed as mean ± SD. The statistical procedures used will be Student’s *t*-test for independent samples (intergroup analysis), paired *t*-test (intragroup analysis), and analysis of variance (ANOVA) for repeated measures to compare both groups at different times. A Pearson correlation will be performed between measures of glucose variability and 8-isoPGF2α/crn. The statistical power will be 90%, and the accepted level of significance will be *P* < 0.01.

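### The planned unadjusted Pearson correlation with 8-isoPGF2α/creatinine cannot by itself show that glucose variability relates to oxidative stress independently of average glucose

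*Protocol article*

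**What the plan says.** Under Statistical analysis plan, the protocol article names one analysis that ties glucose variability to oxidative stress: "A Pearson correlation will be performed between measures of glucose variability and 8-isoPGF2α/crn". It names no covariate for it. The significance level is 1%.

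Under Glucose variability evaluation, the conventional indices (MAGE, variance, CV% and SD) are "all normalized by the mean blood glucose in each period". For the rest the article says "Non-conventional analysis of glucose variability will be conducted using two methods applied to the glucose series" (spectral and symbolic analysis), and it states no normalization for these.

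The motivation is that variability may act beyond the average level. The abstract says: "In addition to the average blood glucose concentration, glycemic variability may be an important factor for the development of chronic diabetes complications". The Background section says the same and names oxidative stress as one pathway: "In addition to the average blood glucose concentration, acute glycemic fluctuations from peaks to nadirs (glucose variability) may be involved". The hypothesis under test is a different matter, namely that "vildagliptin may produce a greater improvement in glucose variability after a submaximal exercise test, compared with glibenclamide".

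**The concern.** Average glucose is a plausible correlate of both variables. A two-variable correlation cannot tell whether 8-isoPGF2α tracks the excursions or the level around which they occur.

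Dividing by the mean looks like an adjustment but is one only in a special case. If excursions grow less than in proportion to the mean, the ratio falls as the mean rises, and anything driven by the mean then correlates negatively with the ratio. If an index is left un-normalized and rises with the mean, the spurious correlation is positive. A real association can also be hidden.

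At stake is how r is read. A positive, null or reversed value could reflect glycemic level alone, while the article's background invites reading it as evidence about variability beyond that level.

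**Working it through.** The article gives no power or sample size for this correlation, so there is no figure of its own to reproduce. Its sample size calculation concerns the between-group MAGE comparison.

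**Inputs from the article.** 20 patients with 10% dropout: 20 × 0.9 = 18 evaluable. Two-sided level 1%.

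**Inputs assumed, not in the article.** CV of mean glucose between patients s_G = 0.20; CV of MAGE s_M = 0.30; MAGE–mean correlation ρ from 0 to 0.7; 8-isoPGF2α–mean correlation λ from 0.5 to 0.7. 8-isoPGF2α depends on mean glucose only, so the true variability effect is zero.

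**Step 1, critical values.** r = t/√(df + t²), with t at the 0.995 quantile.
- Pearson, df 16: 2.921/√(16 + 8.53) = 0.590.
- Partial given the mean, df 15: 2.947/√(15 + 8.68) = 0.606.

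**Step 2, expected spurious r (log-scale approximation).** For MAGE/mean, r ≈ λ(ρs_M − s_G)/√(s_M² + s_G² − 2ρs_M s_G).
- ρ = 0, λ = 0.7: 0.7 × (−0.20)/√0.13 = −0.39 (simulated −0.37).
- ρ = 0.7, λ = 0.7: 0.7 × 0.01/√0.046 = +0.03 (simulated about the same).
- It is zero at ρ = 0.20/0.30 = 0.67.
- Un-normalized MAGE: r ≈ λρ = 0.7 × 0.7 = 0.49 (simulated 0.47).

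**Step 3, false positives at 1%** (40,000 simulated trials per setting, n = 18):

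| Analysis | Range of P<0.01 | Where the maximum lies |
|---|---|---|
| Pearson, MAGE/mean | 1% to 15% | ρ = 0, λ = 0.7 |
| Pearson, MAGE in mg/dl | 1% to 29% | ρ = 0.7, λ = 0.7 |
| Partial given mean | 0.9% to 1.1% | – |

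For MAGE/mean the rate is only about 1% to 2% when ρ is 0.5 to 0.7. It stays below 3% throughout if λ is 0.3.

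**Step 4, CV% divided again.** In a second model SD is proportional to mean^g with residual log-SD 0.25. After k divisions by the mean, r ≈ λ(g − k)0.20/√([(g − k)0.20]² + 0.25²). With λ = 0.5:
- g = 1, k = 1: r = 0, about 1% false positives. Exact proportionality makes one division clean.
- g = 1, k = 2: 0.5 × (−0.20/0.320) = −0.31 (simulated −0.30, 8.5%).
- g = 0, k = 1: the same −0.31 (simulated −0.30, 8.5%).
- g = 0, k = 2: 0.5 × (−0.40/0.472) = −0.42 (simulated −0.40, 18%).

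With λ = 0.7 and g = 0, the rates are 21% for one division and 49% for two.

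**Step 5, masking.** In the second model, give variability a real independent effect (loading 0.6) beside a mean effect (0.5). With g = 0, Pearson on the once-normalized index averages r = 0.15 with 2.5% power, against 64% for the partial correlation. With g = 1 the powers are 54% and 73%.

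**Step 6, a noisy mean.** Suppose longer-term glycemia drives 8-isoPGF2α and MAGE (both correlations 0.7), and the short sensor mean measures it with reliability 0.7. The partial correlation then gives about 4% false positives, against about 2% for Pearson on MAGE/mean. At reliability 0.5 the figures are about 9% and 3%.

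**The case against.** The strongest reply is that the article never promises this conclusion. Its hypothesis and general aim are the drug comparison. Oxidative stress is a secondary outcome, the correlation is neither an aim nor an outcome, and the text on acting beyond the average is hedged background. This stands. A reader might infer that the trial cannot show an effect beyond average glucose and so fails its own rationale. The documents do not support that: the sensor readings and HbA1c needed for an adjusted analysis are collected, and the randomized comparison does not use the correlation.

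A second reply is that a condensed article may leave covariates to a fuller plan. This stands only in part. The article does specify the method, both variables and the form of the conventional indices, and those stated choices are what is at issue.

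A third reply is that the magnitudes are assumed, that the upper figure of 29% belongs to MAGE in mg/dl although the plan normalizes MAGE, and that one division is clean under proportionality. All of this stands. The spectral and symbolic indices were not simulated, so the un-normalized range only illustrates what lack of normalization can do.

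A fourth reply is that the partial correlation's 1% error rate is built into a simulation that generates the marker from the same mean that is then adjusted for. This also stands. Step 6 shows that adjustment is not better in every setting, although with ρ = 0 it still is.

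**Conclusion.** The point holds in a limited form. As specified, the Pearson correlation cannot separate variability from average glucose, and dividing by the mean is not a general substitute for adjustment. Under the assumed inputs, with 18 patients, the false-positive rate at the 1% level is about 1% to 15% for MAGE/mean and 1% to 29% for an un-normalized index. The lower ends are as plausible on the documents as the upper ones, because the article gives no figure for how excursions or 8-isoPGF2α vary with the mean. The double division of CV% rests on the wording taken literally; under it, even exact proportionality does not make that index clean. A reader might also infer that normalization always biases the result, and the calculations contradict that. The vildagliptin versus glibenclamide comparison is untouched.

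**What to change.** In the Statistical analysis plan section, add a partial correlation, or a regression of 8-isoPGF2α/creatinine on each variability index, with the mean sensor glucose of the same recording as covariate. Base any statement about an association beyond average glucose on that result, show the unadjusted r beside it, and label the analysis exploratory. In Glucose variability evaluation, take CV% out of the list of indices to be divided by the mean, since it already is SD over mean. The new sentence should also say which recording is used (before or after treatment).

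No new data are needed, because the normalization already requires the mean, and the article reports that recruitment had not begun. The cost is one degree of freedom: with 18 patients the critical |r| rises from 0.590 to 0.606. The remaining weakness is that each sensor runs for at most 48 hours, so adjustment is incomplete if that mean is a noisy measure of longer-term glycemia. The report should say so.

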## Discussion

Several anti-diabetic agents are available for T2DM treatment. These treatments differ in their mechanism of drug action and their long-term outcomes. In addition to these, non-pharmacological treatments are important, especially exercise, as it is a major tool to achieve target blood glucose and HbA1c. Non-glucose beneficial effects can also be obtained. The many studies reporting the effects of the association between exercise and oral glucose-lowering drugs usually focus on attaining better metabolic control. This study will be conducted to report the glucose variability and cardiovascular responses at rest, during and after submaximal exercise under two oral glucose-lowering drugs (vildagliptin versus glibenclamide).

## Trial status

Not yet recruiting. Enrolment will begin in April 2014. Each patient will have 10 visits to the hospital, and total data collection time will be 16 months.

## Abbreviations

8-iso PGF2 α: 8-iso prostaglandin F2α
ABPM: Ambulatory blood pressure monitoring
BMI: Body mass index
BP: Blood pressure
CGMS: Continuous glucose monitoring system
CV%: Glucose coefficient of variation
DBP: diastolic blood pressure
FMD: Flow-mediated dilatation
GLP-1: Glucagon-like peptide 1
HbA1c: Glycated hemoglobin
HF: High frequency
HRV: Heart rate variability
LF: Low frequency
MAGE: Mean amplitude of glycemic excursion
METG: Metformin plus glibenclamide group
METV: Metformin plus vildagliptin group
NU: Normalized units
PETCO_2_: Tidal carbon dioxide
PETO_2_: End tidal oxygen
PI: Pulse interval
SBP: Systolic blood pressure
SD: Standard deviation
T2DM: Patients with type 2 diabetes
VAR: Glucose variance
VCO_2_: Carbon dioxide production
VE/VO_2_: Ventilatory equivalent for oxygen
VLF: Very low frequency
VO_2_: Oxygen consumption
VO_2peak_: Peak oxygen consumption.
